### Laboratory markers

Laboratory assessments for E/U/Cr, Ca^2+^ and PO_4_^−^, Complete Blood count with NRBC count and NRBC count per 100 white blood cells (WBC) are done at admission using a venous sample. The ratio of NRBC/100WBC is performed by a haematologist. The levels of NRBCs per 100 white blood cells (WBCs) correlates with acute as well as chronic asphyxia and can be used as a reliable marker of perinatal asphyxia and neurological outcome [13, 15].

### Cranial ultrasonography

All participants undergo a cranial ultrasound within 72 h of life looking for structural anomalies and cerebral echo densities. The ventricles are evaluated for size and configurations, the brain parenchyma checked for echogenicity, and presence of cystic encephalomalacia. Any echogenicity within the brain parenchyma, enlargement of the ventricles or the presence of encephalomalacia are considered as abnormal. Cranial ultrasound was chosen for this study over other imaging modalities due to its point of care application, relative affordability and ready availability in our setting. It is more affordable than MRI and is non-ionizing, unlike CT scan. However, it is important to note that it may not be the best tool for assessing intracranial abnormalities in term infants, as the extra-axial structures may not be well appreciated [48]. The cranial ultrasound is repeated at discharge for all participants to enable comparison. The scans are performed by a dedicated sonologist who is blinded to the intervention groups.

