### Sample size and power calculation

There was no previous study in our environment describing the efficacy of EPO administration on the outcome of HIE. Furthermore, there is a paucity of recent published data on mortality and neurodevelopmental impairment from perinatal asphyxia in our environment. Mortality rate from asphyxia was reported to be between 31.1 and 62.8% in some hospitals in Nigeria [5, 9, 10, 44]. Since no study reported the prevalence of neurodevelopmental impairment of asphyxiated babies at 2 years of life, we expected that the prevalence of a combination of the outcome of “death and neurodevelopmental impairment” at 2 years of life among moderate/ severe HIE in a resource-poor environment such as Nigeria should be higher than the prevalence of death only (31.1–62.8%). Thus, we assumed that the prevalence of “death and neurodevelopmental impairment at 2 years of life” among moderate/ severe HIE without EPO treatment in Nigeria will be about 65%. Additionally, Zhu et al. [40] in Zhengzhou, China found that 24.6% (*n* = 18/73) of babies who had EPO either died or had neurodevelopmental impairment while 43.8% who had placebo died or had neurodevelopmental impairment, giving a relative risk of 0.62 (95% CI: 0.41–0.94). Similarly, the range of protective relative risk that was reported or assumed by previous studies was between 0.65 to 0.71 [41, 45]. Hence, we utilized the power calculator in Stata version 16 statistical software (Stata Corp, USA) to calculate the minimum sample size to be 128 babies based on the assumption that 65% of infants with moderate/ severe HIE may likely die or develop neurodevelopmental impairment without treatment; assuming a protective relative risk of 0.6, 80% power and 10% loss to follow -up.

We utilized the Sarnat and Sarnat staging [43] of moderate or severe HIE for the recruitment of eligible participants (Table 2).

**Table 2 Tab2:** Sarnat and Sarnat staging [43] of moderate or severe HIE

Category	Moderate HIE	Severe HIE
1. Level of consciousness	Lethargy or obtunded	Stupor or Coma
2. Spontaneous activity	Decreased	Absent
3. Tone	Hypotonia	flaccidity
4. Posture	Distal flexion	Decerebrate state
5. Primitive reflexes		
a. Suck	Weak or biting	Absent
b. Moro reflex	Incomplete	Absent
6. Autonomic nervous system		
a. Pupils	Constricted	Deviated, dilated, or nonreactive to light
b. Heart rate	Bradycardia	Variable heart rate
c. Respirations	Periodic breathing	Apnoea

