#### Primary outcome measures

The primary outcome is a composite outcome of death or neurodevelopmental impairment at 18–24 months of life. Neurodevelopmental impairment (NDI) is defined as the presence of any one of the following: hypertonia or spasticity, epilepsy, delayed milestones, cerebral palsy, Gross Motor Function Classification System (GMFCS) ≥2, MDAT *Z*-score for age ≤ 1.64 or scores less than expected for age using the MDAT chart [49].

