#### Secondary outcome measures

Survival at discharge and time to discharge. Those that survived to discharge is assessed as: neurologically normal (those who had normal tone and posture, were free from seizures, has established full feed by sucking and have normal neonatal reflexes – rooting, suck, grasp, tonic neck reflex, Moro and stepping reflexes) while neurologically abnormal are those with an abnormal tone and posture, poor suck or any abnormal neonatal reflexes at discharge)Association between the levels of NRBC and NRBC/100WBC with neonatal outcomeCranial USS evidence of ventricular enlargement, parenchymal echogenicity or cystic encephalomalacia.Safety of the medications based on the presence or absence of any adverse event such as:
Hypertension: systolic blood pressure in a neonate which is above 95th percentile for age and sex on three separate occasions;Hypotension: a systolic blood pressure in a neonate which is below the 10th percentile for age and sex on three separate occasionsApnoiec attacksThrombotic events;Polycythemia: venous hematocrit of greater than 65%.Any other adverse effect noted during the hospital stay or follow up.Those with cerebral palsy are further categorized based on features present on standardized neurologic examination, and classified as mild, moderate, or severe, with hemiplegia or diplegia, using the Gross Motor Function Classification System (GMFCS) assessment system.

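### Discharge neurological status and the discharge ultrasound exist only for survivors, so an arm comparison on them is biased against EPO if EPO saves infants of poorer prognosis before discharge

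*Protocol article*

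**What the plan says.** Under Secondary outcome measures, the first item lists "Survival at discharge and time to discharge" and continues: "Those that survived to discharge is assessed as: neurologically normal", with abnormal status defined for the remaining survivors. Cranial abnormality on ultrasound is a separate item with no time point. Table 3 marks both the neurological examination and the ultrasound at discharge, on rows separate from survival.

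Under Cranial ultrasonography, the first scan is for everyone: "All participants undergo a cranial ultrasound within 72 h of life". The second is described in the same terms: "The cranial ultrasound is repeated at discharge for all participants to enable comparison".

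The second specific objective is to compare neurological outcomes between EPO and routine care, first in the newborn period and then at 6, 12, 18 and 24 months. The Data and safety monitoring plan schedules an interim analysis of neonatal outcome.

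On mortality, Sample size and power calculation states: "Mortality rate from asphyxia was reported to be between 31.1 and 62.8% in some hospitals in Nigeria".

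Death enters an outcome definition jointly with impairment only at the end of follow-up: "The primary outcome is a composite outcome of death or neurodevelopmental impairment at 18–24 months of life".

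**The concern.** Survivors to discharge are a subset formed after randomisation. Randomisation makes the arms comparable as whole groups, but not the survivors within them if treatment affects who survives. Suppose EPO keeps alive some infants who would have died under routine care, and those infants more often have abnormal tone, reflexes or scans. They then enter the EPO denominator with no counterparts among control survivors. EPO can look worse at discharge although it harmed nobody, or a real benefit can be hidden.

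The protocol avoids this for the primary outcome by counting death as unfavourable. It does not carry that protection to the discharge outcomes, and its wording for the discharge scan describes a population that cannot be scanned in full.

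**Working it through.** **The plan's own figure.** The sample size section assumes "65% of infants with moderate/ severe HIE may likely die or develop neurodevelopmental impairment without treatment", a relative risk of 0.6, 80% power and 10% loss. The EPO rate is 0.65 × 0.6 = 0.39. With a two-sided 5% test and no continuity correction, n per arm = [1.960 × √(2 × 0.52 × 0.48) + 0.842 × √(0.65 × 0.35 + 0.39 × 0.61)]² / 0.26² = 56.8, rounded up to 57. Then 57 / 0.9 = 63.3, rounded up to 64 per arm, or 128 in all. This reproduces the stated total, so 64 per arm is used below.

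**Inputs from the document.** Mortality m = 31.1% to 62.8%.

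**Inputs assumed, because the document gives none.**
- All of that mortality falls before discharge.
- Mortality relative risk r = 0.8 or 0.6. The protocol uses 0.6 for the composite, not for mortality.
- EPO causes no death that routine care would have avoided.
- Abnormal at discharge: a = 40% in infants who would survive in either arm, b = 90% in infants saved by EPO.

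**Formulas.** Share of EPO survivors who would have died under control: f = m(1 − r) / (1 − m·r). With no true effect in infants who survive either way, the abnormal rate is a in control survivors and (1 − f)·a + f·b in EPO survivors. The spurious difference is therefore f·(b − a) = 0.5·f. If EPO truly lowers a from 40% to 30%, the observed difference is −0.10 + 0.6·f.

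| m | r | Survivors of 64: control / EPO | f | Spurious difference, no true effect | Observed difference when the truth is −10 points |
|---|---|---|---|---|---|
| 31.1% | 0.8 | 44 / 48 | 8.3% | +4.1 points | −5.0 points |
| 62.8% | 0.8 | 24 / 32 | 25.2% | +12.6 points | +5.1 points |
| 31.1% | 0.6 | 44 / 52 | 15.3% | +7.6 points | −0.8 points |
| 62.8% | 0.6 | 24 / 40 | 40.3% | +20.2 points | +14.2 points |

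If r = 1 then f = 0, and if a = b then f·(b − a) = 0. Either condition removes the bias.

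**The same infants with death counted** (r = 0.6, no true effect in infants who survive either way):

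| m | Arm | Normal | Abnormal | Dead | Abnormal among survivors |
|---|---|---|---|---|---|
| 31.1% | Control | 41.3% | 27.6% | 31.1% | 40.0% |
| 31.1% | EPO | 42.6% | 38.8% | 18.7% | 47.6% |
| 62.8% | Control | 22.3% | 14.9% | 62.8% | 40.0% |
| 62.8% | EPO | 24.8% | 37.5% | 37.7% | 60.2% |

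Among survivors EPO looks harmful. Across all three levels it is better: fewer deaths and slightly more normal infants. Merging death with abnormal gives 58.7% v 57.4% and 77.7% v 75.2%, which favours EPO but conceals most of the survival gain. If every saved infant were abnormal (b = 100%), the merged outcome would be identical in both arms.

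**Is a mortality effect plausible under the design?** Deaths cannot exceed the composite, which is assumed to be 39% on EPO. If control mortality at two years were above 39%, the design effect would require fewer deaths. This covers (62.8 − 39) / (62.8 − 31.1) = 75% of the width of the quoted range. It bears on deaths by two years; only those before discharge matter here.

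**The case against.** The strongest reply is that no section prescribes a survivors-only test between arms. The comparison that the discharge scan serves could be first scan against repeat scan, the logistic regression by arm concerns the end of the two-year follow-up, and handling of deaths in secondary outcomes may sit in an analysis plan not shown. Part of this stands: for the scan, a comparison by arm is the natural reading of a secondary outcome but is not spelled out. For neurological status the reply fails, because the specific objectives plan that comparison between arms and the definition restricts it to survivors.

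Secondly, survival at discharge is itself a secondary outcome, so all three levels are already recorded. True, and it makes the repair easy. But two results reported side by side do not remove the bias from the one confined to survivors.

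Thirdly, the sentence about the discharge scan may simply mean all infants who are discharged. That is probably the intent, and the wording should say so.

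Two stronger readings are tempting and unsupported. A reader might infer that a third to two thirds of infants will die, mostly before the second scan. The quoted range is mortality from asphyxia in some hospitals, with no timing relative to discharge and no restriction to moderate or severe disease. A reader might also object that the first scan, taken after dosing may have begun, is a contaminated baseline. The document neither calls it a baseline nor plans an analysis of change from it.

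**Conclusion.** The point holds as a conditional weakness in secondary outcomes. Discharge neurological status is restricted to survivors by definition and the discharge scan by necessity, while a neonatal comparison between arms is planned.

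The bias needs two things: an EPO effect on mortality before discharge, and a worse prognosis in saved infants than in other survivors. Under the assumptions above it is about +4 to +13 points at a mortality relative risk of 0.8 and +8 to +20 points at 0.6. That is enough to cancel or reverse a true 10-point benefit in several of the cases shown. If fewer deaths fall before discharge, the bias is smaller.

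The document does not support saying that the discharge results will be biased, or that the trial's main conclusion is at risk. The primary outcome counts death. The early scan is planned for everyone and is much less truncated by death; the ultrasound item does not say which scan it means.

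**What to change.** 1. For discharge neurological status and for the discharge scan, define the comparison between arms as a three-level ordered outcome in all randomised infants: normal, abnormal, dead before discharge. An ordinal logistic model or a rank test would serve. Report the proportion at each level, because the effect may differ between levels.
2. Show survival at discharge alongside. Prefer the ordered form to a merged death-or-abnormal outcome, which can hide lives saved.
3. Keep survivors-only percentages, labelled descriptive.
4. In Cranial ultrasonography, state that the repeat scan is done in all survivors to discharge.

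Cost: wording and analysis specification only. Survival, examination and scan results are already to be collected, so no visit or measurement is added. The small downside is that the ordered outcome mixes death with examination or imaging findings, which is why the separate levels should always be shown.

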### Outcome

The outcome measures are assessed at different periods (Table 3). Full neurological examination is performed at discharge and at specified intervals (6,12,18,24 months) until the age of 2 years to assess for neurodevelopmental impairments using the Malawi Developmental Assessment Tool (MDAT) which has been validated for African children [49]. Another assessment tool that has been validated for the neurological assessment of neonates is the Bayley Scales of Infant and Toddler Development 3rd Edition.

**Table 3 Tab3:** Outcome measures at different time periods

Domain	Outcome measure	Stage of HIE	T_**1**_ Discharge	T_**2**_ 4 months	T_**2**_ 6 months	T_**3**_ 12 months	T_**4**_ 18 months	T_**5**_ 24 months
Survival	Survival or death	X	X	X	X	X	X	X
Neurologic exam at discharge	Neurologically normal or abnormal	X	X					
Cranial Ultrasonography	Cranial USS abnormality	X	X					
Neurologic examination at clinic visits	Malawi Developmental Assessment Tool (MDAT) scores			X	X	X	X	X
Laboratory levels of EPO, NRBC, and NRBC/100 WBC	Levels of NRBC and NRBC/100WBC in relation to outcome	X	X					
Adverse reactions to EPO	Safety of the medications based on the presence or absence of any adverse event		X	X	X	X	X	X
Gross Motor Function Classification System (GMFCS) assessment system	Those with cerebral palsy are further categorized based on features present on standardized neurologic examination using GMFCS			X	X	X	X	X

T_1−_ T_5 -_ The five time periods for assessment; *NRBC* Nucleated red blood cells, *GMFCS* Gross motor function classification system.

(Bayley III) assessment tool. However, MDAT tool was preferred for this study since it takes cognizance of the culturally relevant differences in the neurodevelopmental assessment of African children. The Paediatric neurologist that assesses the neurodevelopmental status of the children will be blinded to the treatment arms.

#### Primary outcome measures

The primary outcome is a composite outcome of death or neurodevelopmental impairment at 18–24 months of life. Neurodevelopmental impairment (NDI) is defined as the presence of any one of the following: hypertonia or spasticity, epilepsy, delayed milestones, cerebral palsy, Gross Motor Function Classification System (GMFCS) ≥2, MDAT *Z*-score for age ≤ 1.64 or scores less than expected for age using the MDAT chart [49].

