## Methods/ design

### Study design

This study is a double-blind randomized controlled parallel-group trial with one to one allocation ratio. The study is prospectively registered with the PACTR.

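### The MDAT criterion in the primary outcome is printed as Z ≤ 1.64 without a minus sign; as written it would class most unaffected survivors as impaired

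*Protocol article*

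**What the plan says.** All the definitions are in the protocol article, under Primary outcome measures.

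- Endpoint: "The primary outcome is a composite outcome of death or neurodevelopmental impairment at 18–24 months of life".
- Combination rule: neurodevelopmental impairment (NDI) "is defined as the presence of any one of the following". The list covers hypertonia or spasticity, epilepsy, delayed milestones, cerebral palsy, GMFCS of 2 or more, and the MDAT item.
- MDAT item: an MDAT Z-"score for age ≤ 1.64 or scores less than expected for age using the MDAT chart", with a citation for the instrument.

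The planning figures are under Sample size and power calculation. The article assumes that "65% of infants with moderate/ severe HIE may likely die or develop neurodevelopmental impairment without treatment", and it sizes the trial "assuming a protective relative risk of 0.6, 80% power and 10% loss to follow -up". The Study design section gives a "one to one allocation ratio".

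**The concern.** A Z-score limit that is meant to pick out delay should sit in the lower tail. The second half of the MDAT item, "scores less than expected for age using the MDAT chart", confirms the direction: a low score is the bad result. Every other item on the list is also a deficit or an abnormal sign. Yet the printed limit is positive and is joined to a ≤ sign, so it takes in every child from the bottom of the distribution up to about the 95th centile.

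Because one item is enough, the stricter items cannot offset it. A child with no spasticity, no epilepsy and normal motor function would still count as impaired with a Z-score of, say, +1.0. This is the operative definition of the primary endpoint and of the event rate on which the trial was sized, so the sign matters.

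**Working it through.** **Inputs.** From Sample size and power calculation: control rate 0.65, relative risk 0.6, power 80%, loss 10%. From Study design: 1:1 allocation. From Statistical analysis: two-tailed test at 0.05. From Primary outcome measures: cut-off 1.64, any one item sufficient.

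**Assumptions not in the document.** (a) Z-scores are standard normal in unaffected survivors; this is varied in step 5. (b) The planned 65% and 39% are the truly affected infants (dead or impaired), and the rest are unaffected survivors. (c) The printed rule is applied literally.

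**1. The plan's own sample size.** The EPO rate is 0.65 × 0.6 = 0.39, the difference is 0.26 and the mean rate is 0.52.

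n per arm = [1.960 × √(2 × 0.52 × 0.48) + 0.842 × √(0.65 × 0.35 + 0.39 × 0.61)]² / 0.26² = 56.8, so 57.

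Allowing for loss, 57 / 0.90 = 63.3, so 64 per arm and 128 in total. The plan's figure ("calculate the minimum sample size to be 128 babies") reproduces. The sample size is not at fault.

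**2. Share of unaffected survivors flagged.**

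- As printed: Φ(1.64) = 0.9495.
- With a minus sign: Φ(-1.64) = 0.0505.

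**3. Resulting composite.** Observed rate = p + (1 − p) × share flagged.

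| Cut-off | Control | EPO | Difference | RR |
|---|---|---|---|---|
| Z ≤ 1.64 | 0.65 + 0.35 × 0.9495 = 98.2% | 0.39 + 0.61 × 0.9495 = 96.9% | 1.3 points | 0.987 |
| Z ≤ -1.64 | 0.65 + 0.35 × 0.0505 = 66.8% | 0.39 + 0.61 × 0.0505 = 42.1% | 24.7 points | 0.630 |

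**4. Power with 57 analysed per arm, two-sided 0.05.**

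- Planned 65% vs 39%: about 80%.
- Z ≤ -1.64: about 76%, close to the design.
- Z ≤ 1.64: about 7% by the normal approximation. Expected non-events are only 57 × 0.018 ≈ 1.0 and 57 × 0.031 ≈ 1.8, so that approximation is poor. Exact enumeration of the chi-square test gives about 4%.

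**5. Sensitivity of the printed rule to the mean Z of unaffected survivors.**

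| Mean Z | Flagged | Control vs EPO | Power, normal approx. | Power, exact chi-square |
|---|---|---|---|---|
| -1 | 99.6% | 99.9% vs 99.7% | 3% | under 1% |
| -0.5 | 98.4% | 99.4% vs 99.0% | 4% | under 1% |
| 0 | 94.9% | 98.2% vs 96.9% | 7% | 4% |
| +0.5 | 87.3% | 95.5% vs 92.2% | 11% | 10% |
| +1 | 73.9% | 90.9% vs 84.1% | 19% | 19% |

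**6. Consistency with the plan.** In every row the control rate under the printed rule is above 90%, against the 65% assumed. The article's own planning rate therefore does not fit the threshold it prints, and it nearly fits the negative one (66.8%).

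**The case against.** The strongest reply is that this is a dropped character and not a design decision. The same sentence shows that low scores are the adverse direction, and the planned 65% vs 39% cannot come from a +1.64 rule, so the intent can be recovered. This stands as an account of the likely cause. It does not make the printed threshold right: the article states a specific value in the definition of its primary endpoint, and that value points the wrong way.

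A second reply is that the sign may have been lost in text conversion. The minus characters that survive, in Laboratory markers and in the Table 3 footnote, are in superscript or subscript. No signed negative number appears elsewhere in running text to test the point. This cannot be fully excluded, and it is why confirming against the full protocol is an acceptable remedy.

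A third reply is that the power loss needs literal application, and that a paediatric neurologist would not code a child at +1.6 SD as impaired. That is fair. A reader might infer that the trial as run will lose its power, or that children are being misclassified. The document does not show that; it shows only what the published rule would do. Nor would the arms be wholly inseparable, since a gap of about 1.3 points remains in the base case.

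Finally, a reader might infer that the chart limb has no cut-off and would override even a corrected Z limit. The document does not support this. The limb refers to a cited chart that may carry its own threshold. What can be said is that the article does not state that threshold and joins the two limbs by an or.

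**Conclusion.** The concern holds as a wrong threshold in the wording of the primary endpoint, most probably a missing minus sign, with text conversion not ruled out as the cause. It is not an arithmetic fault, and the sample size of 128 is unaffected.

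On a literal reading and under assumptions (a) and (b), the composite would lose almost all its contrast and power would be about 4–7% instead of about 80%. No mean Z tried between -1 and +1 brings it above about 19%. These figures measure why the sign must be right. They do not predict the trial's result, because the coding actually in use is not shown.

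The chart limb is secondary: its limit needs stating so that it and the Z cut-off do not classify the same child differently.

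**What to change.** 1. Correct the criterion to MDAT Z-score for age ≤ -1.64, or confirm against the full protocol that this is the value there and issue a correction to the article if it was misprinted.
2. Check that the case report form and the outcome-coding script use the negative cut-off. Neither is shown, so this is a check; no error in them is alleged.
3. State which limit on the cited MDAT chart counts as less than expected for age, and make it consistent with the Z cut-off.

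The cost is a one-character correction, one clarifying phrase and a short check of the form and the script. No visit, assessment or patient number changes.
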